### **3.6 Circulating tumor DNA and miRNA**

Several studies have shown that detectable circulating tumor DNA (ctDNA) before treatment or after surgical resection is associated with poor prognosis in colorectal cancers.[63, 64] Diehl and his colleagues found that circulating tumor DNA (ctDNA) measurements could be used to reliably monitor tumor dynamics in subjects with colorectal cancer who were undergoing surgery or chemotherapy, suggesting that ctDNA is a promising predictive marker in cancer patients.[65] They concluded that ctDNA seemed more sensitive and reliable than the standard marker, carcinoembryonic antigen (CEA), in the follow-up of patients with CRC. However, the information on using ctDNA to monitor tumor response to multimodality therapy in early or advanced colorectal cancer is limited. In this study we will investigate the feasibility of using ctDNA to monitor tumor response to CRT, and relapse after an apparent complete response.

miRNAs are small single-stranded non-coding RNAs (18-24 nucleotides in length) that negatively regulate their target gene expression by binding to complementary sites in their 3'-UTR. miRNAs play important roles in various biological processes such as development,

differentiation, proliferation, apoptosis, metabolism and morphogenesis, stress response, and diseases, including cancer.[66] In human cancers, miRNAs are deregulated and involved in tumor initiation, progression and metastasis.[67-72] miRNAs are differentially expressed in tumor tissues relative to paired normal controls, and their expression profiles are unique to specific cancer types.[73] miRNA are found in the plasma of cancer patients in a remarkably stable form, due to their binding of the Ago2 protein.[74] A number of studies have investigated the potential role of miRNA as novel biomarkers for early detection, prognosis and therapeutic response of colorectal cancers.[75, 76] In this study, we will use deep sequencing to measure miRNA expression in the tumor and plasma from rectal cancer patients before and after neoadjuvant treatment, and at different points during follow-up, to assess their role as predictors of tumor persistence and as prognostic factors.

### **3.7 Tumor Genotyping**

Genetic profiling of rectal tumors has many potential clinical benefits. Identification of patients whose tumors have a genetic profile indicating resistance to chemoradiotherapy may spare these patients unhelpful neoadjuvant treatment, and they may proceed directly to surgery. On the opposite end of the spectrum, identification of tumors with a genetic profile amenable to a complete clinical or pathological response may help identify patients for whom surgery is unnecessary. We have previously shown that rectal tumors with mutations in both the KRAS and p53 genes are less likely to respond to CRT.[77] DNA polymorphisms have also been associated with rectal cancer response to pCR and toxicity to neoadjuvant therapy.[77, 78] In addition, we found that somatic DNA copy number alterations are associated with tumor response and lymph node metastasis in rectal cancer patients treated with CRT and TME.[79, 80]

Similarly to tumor genotyping, gene expression analysis can be used to predict response of a tumor to chemoradiotherapy. Gene expression analysis is already in clinical use for identification of breast cancer patients who will benefit from adjuvant chemotherapy. Evidence exists that variations in gene expression in rectal cancer may also predict tumor response to neoadjuvant treatment.[81, 82] In this study, we plan to validate these biomarkers of tumor response in a larger group of patients treated with CRT and surgery.

### **3.8 Molecular mechanism of tumor resistance to neoadjuvant therapy**

Residual cancer stem cells are postulated to be a cause of cancer recurrence, as well as a cause of resistance to radiotherapy and chemotherapy. Evidence indicates that cancer stem cells are capable of long-term survival, and have strong regenerative potential.[83] These stem cells also appear to be resistant to ionizing radiotherapy and chemotherapy, due in part to their increased capacity for DNA repair.[84] The crypt base columnar cell (CRC) is one such stem cell. It is located in the crypts of normal colonic and rectal mucosa, and has shown resistance to radiotherapy. CRCs are characterized by exclusive cell surface expression of leucine-rich-repeat-containing G-protein-coupled receptor 5 (Lgr5+), a Wnt target that is often dysregulated in colon cancer.[85] Quantifying CRC within the tumor by immunohistochemical staining for Lgr5+ expression may facilitate the identification of tumor resistance to chemoradiotherapy, while CRC cells within the residual tumor scar in patients with a cCR may indicate that these patients are destined to recur either locally or distantly. Other cell markers postulated to be colonic stem cell markers include CD24, CD44, CD133, CD166, Olmf4, Aldh1, Integrins, Bmi1 and Musashi1.[86]

## **4.0 OVERVIEW OF STUDY DESIGN/INTERVENTION**

## 4.1 Design

This is a multicenter phase II study investigating the efficacy of TNT and selective NOM in patients with LARC. Patients with MRI-staged Stage II (uT3-4, uN-) or Stage III (any T, N+) rectal cancer and would be considered to require a complete TME at baseline will be randomized to receive FOLFOX/CapeOX before (Arm 1 or INCT) or after (Arm 2 or CNCT) 5-FU or capecitabine-based CRT. An interval evaluation will be conducted after completion of INCT in Arm 1, and after completion of CRT in Arm 2. Patients with tumors progression at the time of the interval evaluation will be treated according to standard practice per treating institution guidelines. Those with evidence of stable disease or tumor response will complete neoadjuvant therapy. Patients in both arms will be re-staged after completion of all neoadjuvant therapy. Patients with incomplete response will undergo a TME. Patients with complete or near complete clinical response will be treated with NOM. Criteria for determining complete, near complete and no incompleteresponse are outlined in Section 9.3.2. Patients in both groups (TME and NOM) will be followed according to NCCN guidelines. For study purposes, all patients will be followed for five years from the last date of treatment. For patients in the TME group, last date of treatment will be the date of surgery. For NOM patients, including those who undergo subsequent TME, last date of treatment is the last date of neoadjuvant treatment. Patients in the NOM group will be evaluated using rectal MRI and endoscopic exam (see section 10). Patients in the NOM group who undergo subsequent TME will be followed according to current NCCN guidelines. All patients will be followed based on intent-to-treat. Disease-free survival will be measured after three years.

The study is designed to test the hypothesis that patients with LARC treated with TNT and TME or NOM will have an improved 3-year DFS compared to patients with similar tumors treated with CRT, TME and ACT. We will measure QoL in patients treated with TNT and TME with patients treated with TNT alone. We will also compare INCT to CNCT with respect to organ preservation at 3 years, compliance with treatment, adverse events, and surgical complications.

## 4.2 Intervention

The neoadjuvant chemotherapy regimen is prescribed specifically as 8 cycles of FOLFOX or 5 cycles of CapeOX over a period of approximately 15-16 weeks. The CRT regimen consists of the standard algorithms: a total of 5400-5600 cGy of radiation (4500 cGy to the pelvis, with an integrated boost to the primary tumor and involved nodes of 500 cGy, followed by an optional 400-600 cGy boost to the primary tumor and involved nodes) delivered in 27-28 fractions, respectively, of 180-200 cGy each over a 5-6 week period. Starting on the first day of RT, patients receive 5-FU administered by continuous infusion or capecitabine for the duration of the radiotherapy.

An interval evaluation will be conducted after completion of INCT in Arm 1, and after completion of CRT in Arm 2. Patients with tumor progression at interval evaluation will be treated according to standard practice as per treating institution guidelines; those with evidence of response or stable disease will complete neoadjuvant therapy. Patients in both arms will be re-staged after completion of all neoadjuvant therapy. Those with a clinical response insufficient to warrant non-operative management safely at the time of re-staging evaluation will undergo a TME. Patients with near complete clinical response or clinical complete response will be treated with NOM. Patients in both arms (TME and NOM) will be followed according to NCCN guidelines. Patients in the NOM group will be evaluated using rectal MRIs and endoscopic exam (see section 10). Patients in the NOM group who undergo subsequent TME will be followed according to current NCCN guidelines.

Pathology assessment of the surgical specimens will be performed according to the College of American Pathologists guidelines. Completeness of the mesorectal excision, tumor regression grade (TRG), and tumor staging will be categorized according to the criteria specified in the current edition of the AJCC Staging Manual.[87]

Safety will be assessed by documenting adverse events during TNT and after surgery. Adverse events will be graded according to NCI CTCAE version 4.0, and surgical complications will be graded according to the Clavien-Dindo classification.[88] Refer to Appendix N to see the classification scale.

Tissue and blood samples may be collected from all study patients. When clinically feasible, we will collect tumor tissue at baseline, and tumor and normal tissue samples from patients undergoing a TME. We will also collect blood at baseline and at different time points during and after treatment to measure circulating DNA and miRNA.

## **5.0 THERAPEUTIC/DIAGNOSTIC AGENTS**

### **5.1 Oxaliplatin (OXAL)**

#### **5.1.1 Description**

Oxaliplatin is an organoplatinum complex in which the platinum atom is complexed with 1,2-diaminocyclohexane with an oxalate ligand as a leaving group. Platinum content is 48.1% to 50.1%.

#### **5.1.2 OXAL Drug Preparation/Administration/Dispensing**

The powder is reconstituted by adding 10 ml (for the 50 mg, vials) or 20 ml (for the 100 mg vials) of water for injection, or dextrose 5% in water, which yields a 5 mg/ml solution. This solution is further diluted for infusion with 250 ml to 500 ml dextrose 5% in water. The reconstitution or final dilution must never be performed with a sodium chloride solution. Needles, syringes, catheters, or intravenous administration sets containing aluminum should not be used with oxaliplatin. As with other platinum compounds, contact with aluminum may result in a black precipitate. Oxaliplatin will be administered by intravenous infusion over 120 minutes or according to standard institutional guidelines. Infusion time may be prolonged (up to 6 hours) in patients experiencing pharyngolaryngeal dysesthesia.

#### **5.1.3 Procedure for Handling Drug Spills**

Consult the current OXAL prescriber information for detailed instructions on handling drug spills.

#### **5.1.4 Storage and Stability**

Intact vials should be stored at room temperature. Reconstituted solutions are stable for 24 hours under refrigeration. Solution further diluted in DSW is stable for 6 hours at room temperature or 24 hours under refrigeration.

#### **5.1.5 Source of Drug**

OXAL is commercially available as a multisource product. For this study, locally obtained commercial supplies of OXAL will be used.

### **5.1.6 Drug Accountability**

Because the commercial drug will be used, accounting for OXAL drug supplies is not specifically required in this study.

## **5.2 5-Fluorouracil (5-FU)**

### **5.2.1 Description**

5-FU is a fluoropyrimidine antimetabolite considered to act primarily as an inhibitor of thymidylate synthase. 5-FU is supplied as a colorless-to-faint yellow solution in 10-mL single-use vials. Each 10 mL of solution contains 500 mg 5-FU, with pH adjusted to approximately 9.2 with sodium hydroxide.

### **5.2.2 5-FU Drug Preparation/Administration/Dispensing**

5-FU is administered directly as an IV bolus injection and as a continuous infusion. No dilution is required.

### **5.2.3 Procedure for Handling Drug Spills**

Consult the current 5-FU prescriber information for detailed instructions on handling drug spills.

### **5.2.4 Storage and Stability**

5-FU vials may be stored at room temperature, but should be protected from light.

### **5.2.5 Source of Drug**

5-FU is commercially available as a multisource product. For this study, locally obtained commercial supplies of 5-FU should be used.

### **5.2.6 Drug Accountability**

Because the commercial drug is used, accounting for 5-FU drug supplies is not specifically required in this study.

## **5.3 Leucovorin**

### **5.3.1 Description**

Leucovorin is a mixture of the diastereoisomers of 5-formyl derivative of tetrahydrofolic acid. The active component is the (-)-L-Isomer known as Citrovorum factor. It is useful as an antidote to drugs which act as folic acid antagonists.

### **5.3.2 Leucovorin Drug Preparation/Administration/Dispensing**

Leucovorin may be reconstituted with Bacteriostatic Water for Injection (BWI) or with Sterile Water for Injection. Solutions should be further diluted in DSW, 0.9% NaCl or Ringers solution for infusion over 2 hours. Leucovorin will be administered as a 400 mg/m^2 IV infusion over 2 hours post oxaliplatin administration or according to standard institutional

guidelines. Leucovorin may also be administered concurrently with oxaliplatin, via same infusion lines or according to standard institutional guidelines.

### **5.3.3 Procedure for Handling Drug Spills**

Consult the current Leucovorin prescriber information for detailed instructions on handling drug spills.

### **5.3.4 Storage and Stability**

Intact vials should be stored at room temperature and protected from light. Solutions reconstituted with BWI are stable for at least 7 days at room temperature.

### **5.3.5 Source of Drug**

Leucovorin is commercially available as a multisource product. For this study, locally obtained commercial supplies of Leucovorin should be used.

### **5.3.6 Drug Accountability**

Because the commercial drug will be used, accounting for Leucovorin drug supplies is not specifically required in this study.

## **5.4 Capecitabine (Xeloda®)**

### **5.4.1 Product description**

Capecitabine is an oral prodrug of 5-fluorouracil (5-FU). 5-FU is a fluoropyrimidine antimetabolite considered to act primarily as an inhibitor of thymidylate synthase.

### **5.4.2 Formulation**

Xeloda® is supplied as biconvex, oblong film-coated 500 mg tablets.

### **5.4.3 Storage requirements**

Store tightly closed at 25 degrees C (77 degrees F); stable for brief periods at 15 to 30 degrees C (59 to 86 degrees F).

### **5.4.4 Route of administration**

Tablets should be taken orally within 30 minutes after meals to improve absorption.

### **5.4.5 Source of Drug**

Capecitabine is commercially available as a multisource product. For this study, locally obtained commercial supplies of Capecitabine should be used.

## **6.0 CRITERIA FOR SUBJECT ELIGIBILITY**

### **6.1 Subject Inclusion Criteria**

- Histologically confirmed diagnosis of adenocarcinoma of the rectum.
- Clinical Stage II (T3-4, N-) or Stage III (any T, N+) based on MRI
- Rectal tumor at baseline which would be considered to require complete TME
- No evidence of distant metastases
- No prior pelvic radiation therapy
- No prior chemotherapy or surgery for rectal cancer
- Age  $\geq$  18 years. The minimum legal age of consent for select Canadian provinces is 19
- No active infections requiring systemic antibiotic treatment (oral antibiotics are acceptable at the discretion of the treating physician)
- ECOG Performance status 0-2
- Women with childbearing potential (WOCBP) who are negative for pregnancy test (urine or blood) and who agree to use effective contraceptive method. A woman of childbearing potential is defined as one who is biologically capable of becoming pregnant. Reliable contraception should be used from trial screening and must be continued throughout the study.
- Patients must read, agree to, and sign a statement of Informed Consent prior to participation in this study. Patients who do not read or understand English are eligible and may be consented according to institutional and federal regulations.
- ANC > 1.5 cells/mm^3, HGB > 8.0 gm/dl, PLT > 150,000/mm^3, total bilirubin  $\leq$  1.5 x ULN (except in patients with Gilbert's Syndrome who must have total bilirubin  $\leq$  3.0 x ULN), AST  $\leq$  3 x ULN, ALT  $\leq$  3 x ULN.

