The limited waiver will apply only to MSKCC. Any participating sites that require a limited waiver must obtain it from their own local IRB/Privacy Board (PB) via a separate protocol addendum or request. It is the responsibility of the MSKCC staff to confirm the participating data collection sites(s) have a limited waiver approved by their local IRB(s)/PB(s).

All patients meeting the eligibility requirements will be considered for enrollment regardless of sex, race, or religion. Eligibility criteria may not be waived by the investigator. Discussions regarding protocol enrollment and patient eligibility may begin with any of the investigators named on the protocol or their associates. Patients will be made aware of the protocol, its specific aims and objectives, and the potential risks and benefits that the patient may incur. Patients will be required to read, agree to, and sign an IRB-approved Informed Consent form prior to registration. There will be no financial compensation for patients enrolling in this protocol. Over 120 new patients with stage II or III rectal cancer are treated at MSKCC every year.

The study will be opened at other high-volume rectal cancer centers. The investigators from those institutions have embraced the concepts of TNT and NOM, and demonstrated their ability to accrue, having enrolled over 270 patients to the TIMING trial (PI: [name]). Many of these investigators also accrued to the ACOSOG Z6041 trial (PI: [name]) investigating the efficacy of CRT and local excision in patients with T2N0 rectal cancer.[89] It is expected that approximately 87 patients will be recruited at MSKCC and the remaining 238 will be recruited at the outside centers. Accrual rates are expected to vary across sites based on location and available staff support. Patients will be screened and enrolled at the participating sites. It is recommended that patients have all of their treatment at the primary enrolling site. However, they may receive some of their treatment at affiliated sites. An affiliated site is defined as one that is under the IRB of the enrolling institution.

Please refer to Section 15.0, Research Participant Registration and Randomization Procedures, for details on enrollment procedures.

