| BP                                                                                                                      | normal or increased                                                                                             | normal or decreased                                                                    |
| Treatment                                                                                                               | anxiolytics, observation in a controlled clinical setting until symptoms abate or at the physician's discretion | Oxygen, steroid, epinephrine, bronchodilators; fluids and vasopressors, if appropriate |

Neutropenia has been reported in 73% of patients receiving oxaliplatin with 5-FU and Leucovorin (44% grade 3 or 4). Grade 3 or 4 thrombocytopenia is reported to occur in 4% of patients receiving the combination.

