| Oxaliplatin   | 85                                         | 65                                          | 50                                          | 0                                           |
| Leucovorin    | 400                                        | 320                                         | 260                                         | 260                                         |
| 5-FU bolus    | 400                                        | 320                                         | 260                                         | 260                                         |
| 5-FU Infusion | 1200                                       | 900                                         | 720                                         | 720                                         |

The following tables describe those modifications to be used for Day 1 of a new cycle of FOLFOX therapy and are suggested guidelines for treatment modifications. All dose modifications in a new cycle are based upon the most severe toxicity observed in the previous cycle. Any modifications to treatment should be made at the discretion of the treating physician.

| Dose Modification for Oxaliplatin, 5-FU, and Leucovorin               |                                                                                     |                                                                            |                                                                            |
|------------------------------------------------------------------------------|-------------------------------------------------------------------------------------|----------------------------------------------------------------------------|----------------------------------------------------------------------------|
| Toxicity: CTCAE grade                                                 | Oxaliplatin                                                                  | 5-FU                                                                | LV                                                                  |
| Neutropenia or thrombocytopenia                                       |                                                                                     |                                                                            |                                                                            |

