### **13.0 CRITERIA FOR REMOVAL FROM STUDY**

All patients will be followed for five years from the last date of treatment. Only patients that choose to withdraw consent will be removed from the study and will no longer be followed.

A patient has the right to withdraw from the study at any time for any reason without prejudice to his/her future medical care by the physician or at the institution.

Every effort will be made to evaluate patients for eligibility prior to enrollment. However, if it is discovered that a patient is found to be ineligible after enrollment, the patient will be removed from the study.

Patients may discontinue protocol treatment without being taken off study. Patients who do not complete protocol treatment will remain on study but will be treated at the discretion of their treating physician. Patients placed on the NOM arm who then undergo TME at a later date will remain on study and be followed according to current NCCN guidelines.

If a patient chooses to discontinue treatment, is removed for clinical reasons, and/or received non-protocol treatment, the study team will continue to follow the patient based on intent-to-treat and collect data for up to five years.

Patients may discontinue treatment for any of the following reasons:

1. Unacceptable toxicity, both severe and unexpected
2. Investigator considers it would be in the patient's best interest to not continue
3. Patient is unwilling or unable to continue study treatment
4. Patient becomes pregnant
5. Lost to follow-up

Patients that discontinue protocol treatment must be followed for existing adverse events (AEs) for 30 calendar days after the last day of study treatment. All Grade  $\geq 3$  events considered unexpected and SAEs (as outlined in 17.2) occurring during that period must be reported to the participating site IRB and MSK per section 17.2. These events must be followed up until resolved, unless the condition is unlikely to resolve because of underlying disease, in the treating physician's opinion. After the 30-day period, patients will be followed for disease and survival status for up to 5 years. Limited information about subsequent treatment will be collected and may include chemotherapy, radiation therapy, and clinical exams, and imaging.

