## **16.0 DATA MANAGEMENT ISSUES**

A Clinical Research Coordinator(CRC) will be assigned to the study at each site. The responsibilities of the CRC include project compliance, data collection, abstraction and entry, data reporting, regulatory monitoring, problem resolution and prioritization, and coordination of the activities of the protocol study team. The data collected for this study will be entered into a secured database (Clinical Research Database, CRDBi-Multicenter) at MSKCC. Source documentation will be available to support the computerized patient record. Electronic files with copies of the informed consent, eligibility checklists, adverse events, and outcomes assessments will be kept in a secure institutional network. The study CRC, Clinical Research Supervisor, and the supervising Clinical Research Manager will also have access to these files.

Data collection will principally assess:

- Adherence to eligibility criteria: The study CRC will ensure that all eligibility criteria are met and that the checklist is complete and signed by the consenting professional, prior to initiation of treatment. All supporting source documentation must be maintained in the patient's research file.
- Safety Evaluation: Adverse events (including hematologic and non-hematologic toxicities) will be recorded as they occur, and graded according to the Cancer

Therapy Evaluation Program Common Terminology Criteria for Adverse Events (CTCAE) Version 4.0 (<http://ctep.info.nih.gov>). Toxicities that cannot be graded using the NCI CTCAE v4.0 will be graded as grade 1 (asymptomatic), grade 2 (symptomatic but not interfering significantly with function), grade 3 (causing significant interference with function), grade 4 (life-threatening), or grade 5 (death). For study purposes, reportable non-hematologic events will be limited to Grade  $\geq 3$  diarrhea, Grade  $\geq 3$  neuropathy, Grade  $\geq 3$  DVT, and those events that are Grade  $\geq 3$  and considered unexpected. Reportable hematologic events will be limited to Grade  $\geq 4$  neutropenia/decreased neutrophil count, Grade  $\geq 3$  thrombocytopenia, Grade  $\geq 3$  neutropenic fever (with fever greater than 38.2°C) (outlined in section 17.2). Post-operative complications will be graded according to the Clavien-Dindo classification (see Appendix N).

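### The neutrophil entry limit in protocol section 6.1 pairs a number and a unit that do not fit together; read literally, it excludes essentially no one

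*Protocol*

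**What the plan says.** The last bullet of protocol section 6.1 lists the laboratory limits for entry. It opens with the blood counts, "ANC > 1.5 cells/mm 3 , HGB > 8.0 gm/dl, PLT > 150,000/mm 3"; bilirubin, AST and ALT follow in their own units.

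Two other provisions give the printed figure its force. Section 7.0 states: "Eligibility criteria may not be waived by the investigator". Section 13.0 adds that "if it is discovered that a patient is found to be ineligible after enrollment, the patient will be removed from the study".

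Outside section 6.1, neutropenia appears only as a CTCAE grade (the dose-modification table in 11.7.2 and the reportable events in 16.0) or as a background rate (11.1).

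**The concern.** Neutrophils and platelets are the two entries in the bullet that share a volume unit. One is written out in full and the other is not, so the line cannot be read as using an unstated convention of thousands. Taken as printed, the neutrophil figure is too low to separate one patient from another.

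At stake is a binding entry limit for a myelosuppressive regimen. Section 11.1 reports neutropenia in 73% of patients given oxaliplatin with 5-FU and leucovorin, and grade 3 or 4 in 44%. The trial is multicenter: section 7.0 expects 238 of the 325 patients from outside centers. Each site has to guess the intended figure. An auditor working under section 16.1.1 could not cite the printed text against a patient enrolled with a very low count.

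**Working it through.** The plan derives no figure here that could be reproduced. The check is a unit conversion followed by a search for any other limit.

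**Inputs, both from section 6.1**
- Neutrophils: above 1.5 cells per mm³.
- Platelets: above 150,000 per mm³.

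**Step 1: the printed limit in common units.** Since 1 mm³ = 1 µL, 1.5 cells/mm³ = 1.5 cells/µL. One litre is 10⁶ µL, so this is 1.5 × 10⁶ cells/L = 0.0015 × 10⁹/L, which is effectively zero.

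**Step 2: what it excludes.** Only a patient with essentially no measurable neutrophils fails. The other limits in the bullet are unaffected and still screen.

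**Step 3: size of the discrepancy.** The protocol does not state its intended figure. If a factor of 10³ was dropped (an assumption), the ratio is (1.5 × 10³) / 1.5 = 1,000. Another intention would give another ratio.

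**Step 4: whether another section supplies the limit.**

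| Section | What it provides | Numeric neutrophil limit at entry? |
|---|---|---|
| 6.2 | Exclusion on investigator judgment for concurrent conditions | No |
| 8.1 | Medical and radiation oncology judge suitability for treatment | No |
| 8.2 | Blood count with differential at baseline | No: the test is required, but no limit is set |
| 11.7.2 | Hold-and-resume guidance by CTCAE grade for a new FOLFOX cycle | No |
| 15.1.1 | Laboratory results sent for review at the coordinating center | No: review is against the section 6.1 criteria |
| 16.0 | Grade 4 or higher neutropenia is reportable | No |

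Section 11.7.2 cannot stand in for the entry limit because "All dose modifications in a new cycle are based upon the most severe toxicity observed in the previous cycle". Before the first dose there is no previous cycle, and the tables are offered only as a guide. They also sit oddly beside the printed criterion: they suggest holding a later cycle for grade 2 neutropenia, while section 6.1 read literally sets no effective floor for starting treatment.

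**Step 5: whether the text was lost in conversion.** The documents were read from PDF, so a lost multiplier cannot be ruled out completely. Nothing points to one: the superscript on the unit survived, the word for cells follows the number directly, and there is no gap or redaction mark.

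**The case against.** The strongest reply is that this is an obvious misprint that would mislead nobody. Oncology staff would notice that the figure is implausible and read in a multiplier. Several safeguards would also stop a severely neutropenic patient: the suitability assessment in 8.1, the baseline differential in 8.2, the investigator-judgment exclusion in 6.2, and central receipt of laboratory results under 15.1.1. Section 15.2 further holds randomization of pending registrations until documentation is complete.

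Most of this stands as a limit on the consequence. These safeguards make it unlikely that such a patient would be enrolled and treated. They rest on judgment, however, and do not replace a numeric criterion that may not be waived. Relying on sites to correct the figure silently also leaves each site free to correct it differently.

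Three stronger readings are tempting, and the documents do not support them.
- **That profoundly neutropenic patients will be enrolled, or have been.** The printed number would let them past this one component. The protocol shows no such case, and the safeguards above point the other way.
- **That the comparison of adverse events between arms is biased.** Section 16.0 makes Grade 4 or higher "neutropenia/decreased neutrophil count" reportable, so a count already low at baseline could in principle be recorded as an event. But allocation is randomized, nothing suggests that such patients would favor one arm, and section 14.2 calls the adverse-event comparison exploratory.
- **That the misprint is repeated on the Eligibility Checklist.** Section 15.1 refers to the checklist, but its content is not shown.

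**Conclusion.** The point holds as a wrong entry threshold. Read literally, the neutrophil component of section 6.1 excludes essentially no one, nothing else in the protocol supplies a numeric limit, and the criteria are binding. This rests on reading the section as printed and on no multiplier having been lost in conversion. The 1,000-fold figure rests further on the assumption that a factor of 10³ was omitted.

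The practical risk is small because of the judgment-based safeguards. The sample size, the power and the primary 3-year disease-free survival analysis do not change. It should still be corrected, as a matter of safety screening and of auditable eligibility.

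**What to change.** 1. Reconcile the neutrophil value and unit in section 6.1 and state the figure that the sponsor intended. This review proposes no threshold.
2. Confirm that the Eligibility Checklist carries the same figure and unit.
3. Describe enrolled patients' baseline neutrophil counts against the clarified figure.
4. State in the same amendment that patients already randomized stay in the intent-to-treat analysis whatever step 3 shows. Otherwise the removal rule in section 13.0 could turn a retrospective check into exclusions after randomization, against the intent-to-treat follow-up in sections 1.0 and 4.1.

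**Cost.** The change to the text is one line. The data for step 3 should already exist, because section 8.2 requires a blood count with differential before treatment. The downside is the amendment work. If the correction is treated as making eligibility more restrictive, section 16.3.1 stops a site from enrolling new patients until its own IRB has approved the amendment.
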